## **Intervention**

A randomised controlled trial will be conducted. The experimental group will receive the *SMART* exercise program. To optimise adherence, participants in the *SMART* exercise program will be offered weekly one-on-one sessions with a senior physiotherapist for exercise prescription, monitoring or exercise uptake and potential treatment side effects, and to facilitate behaviour change. The target behaviour of the *SMART* program is to assist participants to build up to or maintain 150 minutes per week of moderate intensity aerobic exercise (or 75 minutes per week of vigorous intensity exercise) as well as two resistance training sessions per week. This target has been informed by the 2019 American College of Sports Medicine (ACSM) guidelines for exercise and cancer. Specific details of the *SMART* program have been described in Section 4 (under Intervention / Product Description).

The principles underpinning the *SMART* exercise program are that it will be:

**Self-determined:** Participants will be in the driver's seat regarding the establishment of weekly goals. They can choose to engage in exercises they enjoy (walking, swimming, cycling, dance etc) at the time of day that suits them best. Due to expected variation in baseline fitness levels and exercise preferences, the program will be individualised to each participant.

**Monitored:** The monitoring of adherence and treatment fidelity will occur through exercise diaries, monitoring of heart rate during the supervised and unsupervised exercise sessions and regular questionnaire data to monitor potential side effects relating to BC treatment and exercise.

**Adaptable:** The participant can choose the days/times they want to exercise and whether the weekly (supervised) session is completed at RPH, or via telehealth. In addition, participants will be briefed to periodise exercise routines according to potential BC treatment side effects (e.g. fatigue, pain, nausea) reported used the above monitoring strategies. Specifically, exercise programs will be adapted if the participant reports any symptoms (e.g. if an individual reports post-exertional malaise for 24 hours following an exercise program and their heart rate reached 140bpm/80% of their predicted HR max, they will be instructed to reduce their heart rate intensity to 110bpm/60% of their predicted HR max for their next exercise session).

**Rehabilitation:** The target behaviour to work towards participation in 150 minutes moderate intensity aerobic exercise per week as well as two resistance sessions, as per the above ACSM guidelines.

**Telehealth supported:** A physiotherapist will offer supervised weekly sessions with each participant via telehealth (or in person at RPH) to supervise exercises, adjust their programs as needed and to implement behaviour change strategies to aid uptake of optimal exercise habits throughout their BC treatment. Participants will also receive email or phone prompts to complete their program on days according to their exercise routine.

Those randomised to the control group will receive usual care. This comprises education regarding the importance of exercise during cancer treatment, a pamphlet and information regarding appropriate off-site exercise groups. In addition, the control group will receive a phone call from the research team once a month. During this phone call, information regarding healthcare utilisation will be collected and participants will receive generic encouragement to stay active during over the 16-week period. The phone call in the control group is important to reduce the potential confounding effect of increased contact (attention) with healthcare professionals in the experimental group.

### 3 Trial Aims / Objectives / Hypotheses

For all research questions, the study population refers to adults with newly diagnosed with breast cancer who are undergoing treatment through the Breast Clinic at RPH.

Primary research questions:

- 1) Does the SMART program, compared with usual care, change health-related quality of life (primary outcome) measured 16-weeks and 12-months following randomisation?
- 2) Does the SMART program, compared with usual care, change peripheral muscle strength, muscle mass, exercise tolerance, exercise adherence and chemotherapy completion rates (secondary outcomes) measured 16 weeks following randomisation?

Secondary research questions:

- 1) Do factors such as adherence, treatment pathway and cancer stage moderate the magnitude of any change in primary or secondary outcomes? (i.e. moderator analysis)
- 2) What is the health care utilisation, absenteeism and presenteeism over the 12 months following randomisation? (descriptive analyses only, to guide patient expectations in regarding these outcomes)

- 3) Does performance on tests of peripheral muscle force-generating capacity and exercise tolerance, change with test repetition (i.e. is there a learning effect)? (can be answered by Honours students enrolled in the BSc physiotherapy at Curtin University)
- 4) What is the minimal detectable difference in health-related quality of life and exercise tolerance? (can be answered by Honours students enrolled in the BSc physiotherapy at Curtin University)
- 5) Do psychological determinants of behavioural change, such as capability, opportunity, and motivation affect adherence to the SMART program and physical activity maintenance?
- 6) Does the SMART program improve mood, and does mood influence adherence to the program and physical activity maintenance?

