## Trial Duration/Schedule

The trial will run over a three-year period, with recruitment commencing in early 2024. Each participant will provide informed consent, after which they will complete a baseline assessment. On completion of the baseline assessments, participants will be randomised to either the experimental or control group and complete a 16-week intervention phase. Thereafter, all participants will complete a suite of re-assessments, (i) mid-way through the intervention phase, (ii) on completion of the intervention phase and, (iii) 12 months following randomisation.

| Milestones                                                           | Timeline        |
|----------------------------------------------------------------------|-----------------|
| 1. Recruit study personnel                                           | July 2023       |
| 2. Complete draft study proposal                                     | November 2023   |
| 3. Submit to ethics/governance                                       | November 2023   |
| 4. Approval obtained from all relevant HREC / RGO                    | February 2024   |
| 5. Commence recruitment (recruitment target = 15 participants/month) | March 2024      |
| 6. Commence intervention                                             | March 2024      |
| 7. Last participant recruitment                                      | March 2026      |
| 8. Complete intervention                                             | July 2026       |
| 9. Complete post-intervention assessments                            | August 2026     |
| 10. Complete long term follow-up assessments                         | March 2027      |
| 11. Data cleaning, analysis and report writing                       | From March 2026 |
| 12. Final study publications and report complete                     | September 2027  |

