## 5 Source and Selection of Participants

### Source of Participants

Participants will be recruited from the outpatient clinics at RPH. Those who appear to meet the study criteria will be identified in the weekly multi-disciplinary Breast Clinic team meetings. A nurse practitioner and/or other BC staff will approach those who meet criteria to share information regarding the trial.

There are some patients who complete radiation treatment prior to being given their script for their hormone medication by the radiation oncologist. The radiation treatment is completed outside RPH as there are no radiation oncology services onsite. For those patients receiving radiation oncology at SCGH, first contact may be made by the treating radiation oncologist to share information regarding the trial. It is noted that although first contact may occur at SCGH, these potential participants sit under the RPH Breast Clinic umbrella, i.e. those who were identified in the weekly RPH multi-disciplinary breast clinic team meetings following breast surgery at RPH but require adjuvant radiation treatment.

Those who express an interest will be contacted by a member of the research team, who will discuss the study with the potential participant. Informed consent will be gained prior to participation in the study.

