### Participant inclusion criteria

Adults will be eligible to participate if they meet the following criteria:

1. Adult with newly diagnosed breast cancer (within the last 6 months)
2. Consent to treatment for their BC, which may include chemotherapy and/or endocrine therapy

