**Exercise tolerance** will be measured as the six-minute walk test (Schmidt 2013). This test will be performed according to standard guidelines (Schmidt 2013). The outcome measured is the distance walked in 6 minutes (6MWD). Each participant will perform the test twice and the longest 6MWD will be recorded as the test result.

**Muscle mass** and body composition will be measured via bioimpedance spectroscopy. This is a non-invasive measure of body composition performed using the SOZO analyser (Impedimed, Brisbane, Queensland). The test takes under a minute, with the participant clothed and standing on the testing platform. The SOZO device is already used in standard care in patient with BC to identify the presence of lymphoedema. This device applies 256 discrete current frequencies through the body, which provides estimates of tissue composition (skeletal muscle mass, fat mass, fat free mass), fluid variables (total body water, extracellular fluid and intracellular fluid), and a metabolic report (cell health, basal metabolic rate and active tissue mass) (Kyle, et al, 2004; Grisbrook, et al, 2015).

**Chemotherapy completion rates** will be extracted from medical records and recorded as a mean relative dose intensity (RDI), which records the actual chemotherapy medication dose intensity as a fraction of the original planned dose intensity, accounting for both the dose and the number of weeks in the chemotherapy cycle (Longo 1991). Any dose adjustments or dose delays will be obtained from the medical records and/or the treating oncologist and the percent of participants requiring dose adjustments or delay will be recorded.

**Psychological determinants of behaviour change** will be measured using; (i) the Capability, Opportunity, Motivation – Behaviour (COM-B; Michie et al. 2011) model factors, (ii) impairment in functioning, (iii) intention, (iv) self-efficacy, (v) habit. These are described below:

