| 6MWT                                                     | X                        |                                                |                                               | X                                                 |                                          |
| Muscle mass                                              | X                        |                                                |                                               | X                                                 |                                          |
| Chemotherapy completion rates                            |                          | X                                              |                                               | X                                                 |                                          |
| COM                                                      | x                        |                                                | x                                             | x                                                 | x                                        |
| WSAS                                                     | x                        |                                                | x                                             | x                                                 | x                                        |
| Intention                                                | x                        |                                                | x                                             | x                                                 | x                                        |
| BTSES                                                    | x                        |                                                | x                                             | x                                                 | x                                        |
| HTQ                                                      | x                        |                                                | x                                             | x                                                 | x                                        |

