## 9 Data Management, Statistical Analysis and Record Keeping

## Statistics and Interim Analysis

*The primary research questions for this study are:*

- Does the SMART program, compared with usual care, change health-related quality of life (primary outcome) measured 16-weeks and 12-months following randomisation?

AND

- Does the SMART program, compared with usual care, change peripheral muscle strength, muscle mass, exercise tolerance, exercise adherence and chemotherapy completion rates (secondary outcomes) measured 16 weeks following randomisation?

The analyses for this research question will be performed according to the intention to treat principle. For the primary outcome, health-related quality of life, with 4 assessment points, linear models will be used to account for repeated measures with participant ID entered as a random effect. The primary time point of interest will be the end of the intervention phase. Group, time and group by time will be analysed as fixed effects and the baseline measure will be entered as a covariate to adjust for random baseline differences. Between group difference for the dependent outcome of chemotherapy completion (yes/no) will be analysed using logistic regression. Between group differences for the remaining secondary measures (peripheral muscle force-generating capacity, muscle mass, exercise tolerance) will be examined using linear regression with the corresponding baseline measure used as a covariate. Data transformations or alternative models (such as gamma distribution) will be considered if there is poor model fit.

Missing data will be examined and multiple imputations investigated (assuming they are missing at random). Models will be adjusted for covariates, randomisation variables and confounders such as age. Estimates of the effects will be reported with their corresponding 95% confidence intervals.

*The first secondary research question is:*

- Do factors such as adherence, treatment pathway and cancer stage moderate the magnitude of any change in primary or secondary outcomes? (i.e. moderator analysis)

To understand any moderator effects, the listed covariates will be entered into a multivariable model using the outcomes listed above. In addition, adherence will be examined to see if it mediates the relationship with the outcomes, by calculating the indirect through the use of partial coefficients.

*The second secondary research question is:*

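### Chemotherapy completion (yes/no) is read at a fixed 16 weeks after randomisation, but entry is not tied to any point in chemotherapy, so courses still running are misclassified and doses given before randomisation may dilute the effect

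*Protocol*

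**What the plan says.** **When it is read.** The second primary research question in section 3, repeated in section 9, concerns "exercise adherence and chemotherapy completion rates (secondary outcomes) measured 16 weeks following randomisation". In the timing-of-outcomes table (section 7, Efficacy assessment), the row "Chemotherapy completion rates" is marked weekly during the intervention phase and at its end. It has no mark before randomisation and none at 12 months. The phase lasts 16 weeks and follows the baseline assessment (Trial Duration/Schedule): "participants will be randomised to either the experimental or control group and complete a 16-week intervention phase".

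**Who enters.** Inclusion criterion 1 is "Adult with newly diagnosed breast cancer (within the last 6 months" (the bracket closes there). Criterion 2 is "Consent to treatment for their BC, which may include chemotherapy and/or endocrine therapy". Neither criterion, nor any exclusion, refers to chemotherapy being not yet started, under way or finished. Source of Participants expects some people to be approached late in their pathway: "There are some patients who complete radiation treatment prior to being given their script for their hormone medication by the radiation oncologist".

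**How it is measured.** Section 7 uses mean relative dose intensity, which "records the actual chemotherapy medication dose intensity as a fraction of the original planned dose intensity". It also records the percentage of participants whose doses were adjusted or delayed. No start or stop date relative to randomisation is given.

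**How it is analysed.** Section 9: "Between group difference for the dependent outcome of chemotherapy completion (yes/no) will be analysed using logistic regression". There is no rule for a course still running at week 16.

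**The concern.** The clock for this outcome starts at randomisation, but the course of chemotherapy does not. Two problems follow.

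1. *Cut-off at week 16.* A patient on schedule in a course that ends after week 16 has not completed at the reading, and neither has one who stopped early. Under a yes/no variable both are scored no. The same happens to a patient whose course was due to end by week 16 but slipped past it because of a delay, which section 7 itself anticipates.
2. *Dose window not anchored.* Section 7 compares actual with planned dose intensity but does not say from when. For a patient randomised part-way through a course, doses already given may count. SMART cannot have changed them, so they pull the two arms together.

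The background section cites better chemotherapy completion as part of the case for exercise. A null result on this outcome could partly reflect the calendar.

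**Working it through.** **The protocol's own figures.** None is given for chemotherapy completion. The only sample size is for quality of life: 2 × (1.96 + 0.8416)² × 20.52² / 8² = 103.3, so 104 per group, and 104 / 0.80 = 130. These reproduce but do not bear on this point.

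**Inputs from the protocol.** Reading at week 16 after randomisation (section 3); entry up to 6 months after diagnosis, which is 6 × 52 / 12 = 26 weeks (section 5). The entry window is longer than the 16-week phase, so a course can lie partly or wholly before randomisation.

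**Assumptions.** The protocol gives neither course length nor start date. Let L be the planned course length in weeks and s the start week relative to randomisation (negative means before it). Dose is taken as spread evenly over the course.

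- Share before randomisation = min(L, max(0, −s)) / L
- Share after week 16 = min(L, max(0, s + L − 16)) / L
- Share inside the window = the remainder

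| L | s | before | inside | after week 16 |
|---|---|---|---|---|
| 12 | −12 | 100% | 0% | 0% |
| 12 | 0 or +4 | 0% | 100% | 0% |
| 12 | +6 | 0% | 83% | 17% |
| 16 | −8 | 50% | 50% | 0% |
| 16 | 0 | 0% | 100% | 0% |
| 16 | +4 | 0% | 75% | 25% |
| 18 | −8 | 44% | 56% | 0% |
| 20 | 0 | 0% | 80% | 20% |
| 24 | −4 | 17% | 67% | 17% |
| 24 | 0 | 0% | 67% | 33% |
| 24 | +4 | 0% | 50% | 50% |

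(Rounded. For example, 4/20 = 20% and 8/24 = 33%.)

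The range includes cases with no misalignment: 12 weeks starting at week 0 to 4, and 16 weeks starting at week 0, provided nothing is delayed.

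**Effect of the cut-off on yes/no.** Any row with a positive last column is scored no at week 16, however well treatment went. Let a fraction f of chemotherapy patients in each arm be in that position, and let the true completion probabilities be p₁ and p₀ whatever the course length. The observed difference is then (1 − f)p₁ − (1 − f)p₀ = (1 − f)(p₁ − p₀). It shrinks in proportion to f, which the protocol does not allow us to estimate.

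**Effect of earlier doses on RDI, if they count.** If SMART acts only on doses after randomisation, a whole-course RDI effect is the true effect times the share from randomisation on. For L = 16 and s = −8, an assumed 6-point effect appears as 6 × 0.5 = 3. If that share applied to everyone, equal power would need 1/0.5² = 4 times the sample; at a 75% share, 1/0.75² = 1.8 times.

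**If earlier doses do not count.** The timing table, with no mark before randomisation, could be read that way. Section 7 then gives no matching denominator. If the full planned dose stays below the line, the same fully treated patient (L = 16, s = −8) could score no more than 50%.

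**The case against.** Several points on the other side are sound.

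- A reader might infer that doses before randomisation definitely count. The protocol does not say so. It is a natural reading of RDI against the plan as first made, but the timing table has no mark before randomisation. If doses in the phase were scored against the plan for the same weeks, this dilution would not arise. What stands is that the window is not stated.
- A reader might also infer that RDI is scored against the whole course. Those words are not there. Dose intensity is dose per unit time and can be computed to date, so a patient on schedule at week 16 of a 24-week course can have an RDI of 1.0. The cut-off problem therefore belongs to the yes/no variable in section 9, not to RDI as such.
- It is tempting to say that the trial cannot answer its question on chemotherapy completion, or that the result is biased between arms. Randomisation balances start times on average, treatment pathway is a stratification factor, and the models adjust for the randomisation variables. Pathway does not separate chemotherapy not started, under way and finished, but that costs precision and does not favour one arm. The percentage with dose adjustments or delays can also be reported without a finished course.
- Numerator and denominator rules are often left to a statistical analysis plan, and one is promised. That covers part of the RDI window. It does not cover the fixed week-16 reading with nothing later, which the protocol sets in its research question and its timing table.
- This is a secondary outcome with no sample-size calculation behind it. That limits the weight of the point.

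**Conclusion.** The point holds in limited form. Followed as written, the protocol reads a yes/no completion outcome at week 16 for patients whose courses may begin or end at any time relative to randomisation. Unfinished and abandoned courses are then mixed. Separately, the RDI window is not tied to randomisation, so doses SMART could not affect may enter the score.

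The size depends on assumed timing. The share of a course after the cut-off is nil for an undelayed course of 16 weeks or less begun at randomisation, 20% for 20 weeks and 33% for 24 weeks. The share before randomisation runs from 0% to 100% across the cases examined. How many patients fall into each case cannot be derived from the protocol. The expected harm is dilution and misclassification in a secondary outcome, with no direction favouring either arm. The change is worth making because it is cheap.

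**What to change.** Amend section 3, the chemotherapy paragraph and timing table in section 7, and the matching text in section 9:

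1. Define RDI and completion over the doses still planned on the day of randomisation, with the same window for numerator and denominator. Patients with no doses left to receive at that date then fall outside this analysis by a rule fixed at baseline, which keeps the randomised comparison intact.
2. Extract medical records to the planned end of that course plus any delays, within the existing 12-month follow-up, instead of stopping at week 16. Add the later extraction to the timing table.
3. Record at baseline the date chemotherapy started or is due, and the number of cycles remaining.

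The cost is protocol wording, two baseline fields and a later look at records that are already the data source. No treatment or visit changes. The outcome becomes available after week 16 for some patients, and for them it covers doses given after the supervised phase has ended, so the research question should no longer describe it as a 16-week measure.
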